### Provisions for post-trial care {30}

All participants will return to usual care after the trial. As part of our safety protocol, we will monitor the self-reported questionnaires measuring depression, anxiety, and stress (DASS-21). Any participants with scores above the “severe” threshold will be contacted by the site coordinator who will indicate concern, ask if they would like help/support, and offer to facilitate this through contact with the treatment team who would manage referrals (the thresholds we will use are: depression subscale ≥ 11, anxiety subscale ≥ 8, and stress subscale ≥ 13).

### Outcomes {12}

#### Primary outcome

(M1) Proportion of participants who are diagnosed with a subsequent new primary or recurrent melanoma (any stage) at a fast-tracked unscheduled clinic visit during the 12 months follow-up after randomisation Melanomas are histologically confirmed and centrally reviewed by the trial dermatopathologist (RAS), who will be blinded to study arm. Classification of a visit as fast-tracked unscheduled vs routinely scheduled will be done by the endpoint adjudication committee based on the participant’s clinic letters, blinded to study arm.

#### Secondary outcomes

(M2) Time to diagnosis of a new skin cancer: time from randomisation to the histopathology diagnosis of a melanoma or keratinocyte skin cancer (as defined by the date on the histopathology report).

(M3) Pathological characteristics of new skin cancers: including thickness, stage, and other prognostic factors (melanomas and keratinocyte skin cancers).

(M4) Skin Self Examination (SSE) including:

M4.1. Thoroughness, confidence, beliefs, attitude, and knowledge of SSE will be assessed by items adapted from Janda et al. [42].

M4.2. Adherence with recommended SSE practice (total body self-examination conducted three-monthly); Participants will be asked how often they perform a complete examination of their skin.

(M5) Fear of new or recurrent melanoma (FCR) severity: assessed using a modified (i.e. melanoma-specific) version of the 9 item FCR Inventory severity subscale, the most comprehensive multi-dimensional scale of FCR available [10]. A higher score indicates greater FCR.

(M6) General anxiety, stress and depression: measured using the short version of the Depression Anxiety and Stress Scales (DASS-21) [43]. The DASS-21 is a set of three 7-item self-report scales designed to measure the emotional states of depression, anxiety, and stress.

(M7) Acceptability of hypothetical reduction in scheduled clinic visit frequency: measured through questionnaire items designed specifically for this study.

(M8) Number of lesions surgically evaluated: measured through interrogation of clinic data.

(M9) Number of clinic visits attended: (routinely scheduled and fast-tracked unscheduled clinic visits) measured through clinic data.

(M10) Resource use: Costs to the health system and to patients in each arm of the trial will be estimated using an online resource use diary. The diary will be used to document and measure health service use - such as doctors’ clinic visits, other health practitioner consultations, imaging and other tests, hospital visits, and time taken to take and submit images for teledermatology. The diary will also document days out-of-role (including paid and unpaid work) and travel costs. The diary will be based on existing resource use questionnaires and the patient diary used in the MEL-SELF pilot study.

(M11) Carbon emissions: carbon costs of resources used, estimated using established carbon accounting methods [35, 36].

(M12) Qualitative results: telephone interviews with a sub-set of intervention group participants at baseline, 6 months and 12 months after randomisation and control group participants at 12 months to explore, in depth, patients’ experiences from participation in the trial. We will also interview clinicians to explore their experience of the benefits and limitations of the intervention. A protocol for the nested qualitative study is included in Supplementary file 3.

(M13) Technical performance of dermatoscopes: participant ability to submit images (adherence with 3 monthly image submission), participant satisfaction with dermatoscope, quality of the images (measured using a checklist developed and tested in another teledermatology study [44]), any device deficiencies reported.

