**Methods:**

Stage 0/I/II melanoma patients (*n* = 600) from dermatology, surgical, or general practice clinics in NSW Australia, will be randomised (1:1) to the intervention (patient-led surveillance, *n* = 300) or control (usual care, *n* = 300). Patients in the intervention will undergo a second randomisation 1:1 to polarised (*n* = 150) or non-polarised (*n* = 150) dermatoscope. Patient-led surveillance comprises an educational booklet, skin self-examination (SSE) instructional videos; 3-monthly email/SMS reminders to perform SSE; patient-performed dermoscopy with teledermatologist feedback; clinical review of positive teledermoscopy through fast-tracked unscheduled clinic visits; and routinely scheduled clinic visits following each clinician’s usual practice. Clinician-led surveillance comprises an educational booklet and routinely scheduled clinic visits following each clinician’s usual practice.

The primary outcome, measured at 12 months, is the proportion of participants diagnosed with a subsequent new primary or recurrent melanoma at an unscheduled clinic visit. Secondary outcomes include time from randomisation to diagnosis (of a subsequent new primary or recurrent melanoma and of a new keratinocyte cancer), clinicopathological characteristics of subsequent new primary or recurrent melanomas (including AJCC stage), psychological outcomes, and healthcare use. A nested qualitative study will include interviews with patients and clinicians, and a costing study we will compare costs from a societal perspective. We will compare the technical performance of two different models of dermatoscope (polarised vs non-polarised).

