#### Secondary objectives

To assess the impact of patient-led vs clinician-led surveillance on:
Time from randomisation to diagnosis of a subsequent new primary or recurrent melanoma and of a keratinocyte cancer.Psychological outcomes using validated scales for fear of new or recurrent melanoma, general anxiety, stress, and depression.Skin self-examination:I.confidence in, knowledge of, attitudes to, and beliefs about skin self-examination;II.adherence to recommended skin self-examination practice.4.Acceptability of a reduction in routinely scheduled clinic visit frequency.5.Resource use through measurement of:I.number of lesions surgically excised;II.number of follow-up visits attended (both scheduled and unscheduled).

And to:
6.Evaluate the technical performance of two different models of mobile dermatoscope, which patients can attach to their smartphones.7.Assess the acceptability of patient-led surveillance to patients and clinicians (nested qualitative study).8.Assess resource use and costs for healthcare system, patient, and environment (costing study).

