### Sample size {14}

Assuming that 6–8% of patients in the clinician-led surveillance group have a subsequent new primary or recurrent melanoma diagnosed within the 12 months follow up [21, 45] and that 1% have a diagnosis through a fast-tracked unscheduled clinic visit, we will need to recruit at least 452 participants (226 to patient-led surveillance and 226 to clinician-led surveillance) in order to have at least 80% power to detect a 5% absolute increase in the patient-led surveillance group (i.e. 6% have new or recurrent melanoma diagnosed through unscheduled visit at treatment centre). Assuming up to 25% of study participants withdraw consent or dropout, we will recruit 600 participants (300 to patient-led surveillance and 300 to clinician-led surveillance). These calculations assume a two-sided 5% significance level and were done using Fisher’s exact test. This sample size will also ensure at least 80% power to detect a hazard ratio of 1.71 for time from randomisation to diagnosis of a skin cancer for the patient-led vs clinician-led surveillance groups (due to earlier and increased detection in the patient-led group). This calculation assumes a 20% event rate in the clinician-led surveillance group [21, 45] (60 events among 300 control participants), a 32% event rate in the patient-led surveillance group (96 events among 300 intervention participants), and 26% event rate overall (156 events among 600 trial participants).

For the nested qualitative study, we will aim to recruit 30–45 participants, which may vary depending on the saturation of themes but is a sample size commonly sufficient to reach saturation in themes and topics [46].

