##### End of study

Active participation will continue for 12 months following randomisation or until all trial tasks have been completed (end dates will be staggered for individual participants and they will not be able to submit data after they have finished the 12 months follow up). We will collect linked data from the clinics, Cancer Registry and Medical Benefits Scheme for a further 12 months post-trial (i.e. 24 months post-randomisation).

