##### Secondary outcomes

We will assess the effect of patient-led and clinician-led surveillance on the secondary outcome of time to diagnosis of a skin cancer (melanoma or keratinocyte cancer), using Cox proportional hazards models. We will present unadjusted and adjusted analyses. For the latter, we will include the same covariates as for the primary outcome (important prognostic variables for outcome event). We will check the proportional hazards assumption using visual inspection of plots (including Schoenfeld residuals) and corresponding test statistics. Other assumptions to be checked include if there is non-informative censoring and if there is a secular trend. All participants will continue to be followed up unless they have withdrawn their consent or moved interstate. In the case that they have withdrawn their consent or moved interstate, participants will be censored at the last available follow-up. The unadjusted and adjusted hazard ratios with 95% CI and *p* values will be reported. If the assumptions including the proportional hazards assumptions are violated, these will be addressed as required. The time to diagnosis will also be analysed allowing for competing risk of death.

The appropriate generalised linear model will be used to assess the remaining secondary outcomes. In general, Poisson regression will be used for count variables, logistic regression for proportions and multiple linear regression for continuous outcome variables. We will assess effects on continuous outcomes (adherence with SSE; thoroughness, confidence, beliefs, attitude and knowledge of SSE; level of fear of new or recurrent melanoma; general anxiety, stress and depression; and acceptability of reducing the frequency of routinely scheduled clinic visits) by including baseline measurement of the outcome as well as other relevant prognostic variables as covariates in the multiple linear regression model. For example, for the outcome: level of fear of new or recurrent melanoma severity, we will include baseline measurement of FCRI severity subscale and personal history of depression or anxiety as covariates. We will estimate the between-group difference in change from baseline for each outcome, together with 95% CI and *p* values. We will check the appropriate model assumptions and if any are violated, then we will use other generalised linear models.

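### The objective names time to melanoma and time to keratinocyte cancer separately, but the outcome, Cox model and power statement use one pooled event, so no outcome stated in the protocol compares any-visit melanoma detection between arms

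*Protocol article*

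**What the plan says.** Two places in the protocol article name two targets. The abstract lists "time from randomisation to diagnosis (of a subsequent new primary or recurrent melanoma and of a new keratinocyte cancer" among the secondary outcomes, and the first secondary objective reads "Time from randomisation to diagnosis of a subsequent new primary or recurrent melanoma and of a keratinocyte cancer".

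Three places use one pooled event:
- M2, under Outcomes {12}: "time from randomisation to the histopathology diagnosis of a melanoma or keratinocyte skin cancer".
- The secondary-outcome analysis in Statistical methods {20a}: "time to diagnosis of a skin cancer (melanoma or keratinocyte cancer), using Cox proportional hazards models". The only competing risk named there is death.
- Sample size {14}: "at least 80% power to detect a hazard ratio of 1.71 for time from randomisation to diagnosis of a skin cancer", with 20% of controls and 32% of the intervention arm having an event (60 and 96 of 300, 156 in all).

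The same sample size section puts melanoma in the control arm at 6–8% over 12 months, with 1% diagnosed at an unscheduled visit. The primary outcome M1 is restricted by route: "melanoma (any stage) at a fast-tracked unscheduled clinic visit during the 12 months follow-up after randomisation". M3 covers "Pathological characteristics of new skin cancers: including thickness, stage, and other prognostic factors (melanomas and keratinocyte skin cancers", which describes cancers once they are found.

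**The concern.** The objective and the outcome do not match. An analyst who follows M2 and the Cox paragraph as written would report one hazard ratio for any skin cancer and leave the melanoma half of the objective unanswered.

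The other listed outcomes do not fill the gap. M1 leaves out melanomas found at scheduled visits. M3 concerns features of diagnosed cancers. M8 and M9 count lesions evaluated and visits attended. The Pathology section has staff record the numbers of melanomas and keratinocyte cancers, but no stated analysis compares the melanoma numbers or dates between arms.

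The Discussion says the trial will show whether patient-led surveillance allows earlier detection of melanoma and of keratinocyte cancers. A pooled result cannot say which of the two was affected. If the event is the first skin cancer, which is the natural reading of a Cox model for this outcome although M2 does not spell it out, a keratinocyte cancer early in follow-up also hides a later melanoma in the same person.

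**Working it through.** **1. Is the event really pooled, or is 'or' loose wording?** The sample size section gives melanoma as 6–8% of controls and the M2 event as 20%. A 20% rate cannot be melanoma alone, so the powered event is the pooled one.

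**2. The plan's own power figure.** Inputs from Sample size {14}: 156 events, HR 1.71, two-sided 5%, 1:1 allocation. Schoenfeld's formula is

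power = Φ(√D × ln(HR)/2 − 1.96).

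- D = 156: √156 × 0.5365/2 − 1.96 = 1.39, power 91.8%.
- D = 117 (25% fewer events): power 82.7%.
- HR implied by 20% against 32%: ln(0.68)/ln(0.80) = 1.73, close to the stated 1.71.

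The statement of at least 80% holds for the pooled event.

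**3. How much of the pooled event is melanoma?** Every participant with a melanoma has a pooled event. Taking the 20% as a 12-month rate (the protocol does not date it), the share of control participants with a pooled event who have a melanoma is 6/20 = 30% to 8/20 = 40%. The share whose *first* event is a melanoma cannot be higher. The remaining 60–70% have keratinocyte cancer only.

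**4. Illustration (assumed, not in the protocol).** Hold melanoma at 7% in both arms. Participants with keratinocyte cancer and no melanoma are then 20 − 7 = 13% of controls. If they became 32 − 7 = 25% of the intervention arm, the pooled event would go from 20% to 32%, the full planned effect, with the proportion with melanoma unchanged. With melanoma at 6% or 8%, the keratinocyte-only figures are 14% to 26%, or 12% to 24%. The protocol gives no separate keratinocyte rate, so this shows what M2 permits and is no forecast.

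**5. Melanoma alone.** Assume HR 1.71 carries over to melanoma, which the protocol does not say. With control rate p, the intervention rate is 1 − (1 − p)^1.71, and D is n per arm times the sum of the two rates.

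| Control rate | Intervention rate | Events, 300 per arm | Power | Events, 225 per arm | Power |
|---|---|---|---|---|---|
| 6% | 10.0% | 48.1 | 46% | 36.1 | 36% |
| 8% | 13.3% | 63.9 | 57% | 47.9 | 46% |

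With 300 per arm, the HR detectable with 80% power is about 2.13 at a 6% control rate and 1.96 at 8%. The 225-per-arm columns treat the 25% lost as contributing no events.

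**The case against.** **The analysis plan may split M2.** The protocol defers the full statistical methods to a separate plan that is not shown. This stands as a limit: a reader might infer that the trial has no planned melanoma comparison at all, and the document supports only that this protocol states none. It does not remove the mismatch. A plan that follows M2 leaves the objective unanswered, and a plan that splits it departs from M2.

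**The power statement is accurate.** A reader might infer that the trial claims 80% power for melanoma. It does not: the 80% is tied to a skin cancer at a 20% control rate. Nor does a secondary outcome need its own power. Both points stand.

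**The visit route is the declared primary target.** A reader might go further and call a positive M1 empty re-routing. M1 could indeed rise from 1% to 6% within an unchanged melanoma total of 6–8%. But the primary objective is explicitly about detection at unscheduled visits, and the stated rationale is that fewer routine visits might then be possible. With scheduled visits 6 to 12 months apart, a melanoma that moves to an unscheduled visit may well be found sooner. The document does not support calling M1 defective; it shows only that M1 does not measure total detection or its timing.

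**Keratinocyte cancer is a stated target too.** This is correct, so a pooled result is not off-target. It still cannot answer for each cancer, which is what the objective asks.

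**The loss scenario is harsh.** Withdrawn participants may consent to passive registry and clinic follow-up, and the Cox analysis censors rather than deletes. The 36–46% is therefore the low end.

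**Conclusion.** The concern holds as an internal contradiction. The abstract and objective name two endpoints, while M2, the Cox analysis and the power statement use one. As written, no outcome in this protocol compares any-visit melanoma detection or its timing between arms, and only about 30–40% of control participants with the pooled event would have a melanoma.

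The pooled power is right (about 92% at 156 events). A melanoma-only analysis would have about 46–57% power with all 600 participants, or 36–46% if a quarter contribute no events. These figures rest on HR 1.71 applying to melanoma and on the protocol's 6–8% rate. The mismatch should be corrected. It does not threaten the primary analysis or the sample size.

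**What to change.** Align M2 and the Cox paragraph with the objective by defining:
- (a) time to first melanoma at any visit type, with follow-up continuing past any keratinocyte cancer;
- (b) time to first keratinocyte cancer, with follow-up continuing past any melanoma;
- (c) the existing pooled event, kept as the powered analysis.

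Give (a) and (b) each a Cox model and a 12-month cumulative incidence, with death as the competing risk as already planned. Do not censor one cancer at the other: neither prevents the other from being diagnosed later, and censoring would bring back the masking. Report melanomas by scheduled and unscheduled route in each arm, so that M1 can be read beside the total.

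Optionally, repeat (a) on the linked data to 24 months after randomisation ("We will collect linked data from the clinics, Cancer Registry and Medical Benefits Scheme for a further 12 months post-trial"), which would help to separate earlier from additional detection.

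The cost is a wording change and a few more models. Diagnosis dates come from histopathology reports, and the two cancer types are already recorded separately. The drawback is a wide interval for melanoma, which the text should acknowledge.

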## Introduction

### Background and rationale {6a}

Melanoma incidence continues to increase in many countries worldwide. In Australia, the total number of people diagnosed with new melanomas increased from 3526 in 1982 to 14,485 in 2016, and the age-standardised rate increased from 27.9 per 100,000 in 1982 to 54 per 100,000 in 2016 [1]. This appears to be largely driven by increased early detection of early-stage melanoma before it has spread from the skin (in situ (stage 0) melanoma, and stage I–II invasive melanoma, together > 95% of all new melanoma diagnoses in Australia) [2]. After surgical excision of the melanoma, these patients are at risk of developing a subsequent new primary melanoma, a recurrence of their treated primary melanoma, and new keratinocyte (non-melanoma) skin cancers. Therefore, it is typically recommended that they undergo at least 10 years follow-up (and often longer), at intervals ranging from 3 to 12 months depending on melanoma stage [3, 4]. Patients diagnosed with an early-stage melanoma have a very good prognosis in terms of life expectancy: those with melanoma in situ (stage 0) have the same mortality risk as the general population, and those with thin melanomas (< 0.8 mm, which accounts for 65% of all invasive melanomas) have a 20-year survival of 80–96% [5–7]. Clinician-led surveillance in the form of routinely scheduled clinic visits is widely accepted as the usual model of follow up care after removal of a melanoma, under the assumption that this leads to earlier detection and treatment a subsequent new primary or recurrent melanoma, and reduced mortality. However, there is no direct evidence that clinician-led surveillance leads to improved survival [4, 8].

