### Statistical methods

#### Statistical methods for primary and secondary outcomes {20a}

A detailed Statistical Analysis Plan will be published separately with a full description of the statistical methods that will be used for analysing the primary and secondary outcomes, planned additional assessments including subgroup and sensitivity analyses, and methods to manage missing data (manuscript in preparation). All analyses will adhere to the intention-to-treat principle, unless otherwise stated. As a secondary analysis, we will also estimate the effect that would have been observed had all participants adhered to the protocol.

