## Discussion

This randomised controlled trial will compare patient-led surveillance -with clinician-led surveillance for patients with a history of early-stage melanoma. It will generate evidence on whether patient-led surveillance can safely and effectively enable earlier detection of subsequent new primary or recurrent melanoma and keratinocyte cancers. It will also provide evidence of the acceptability of patient-led surveillance to patients and clinicians and report on the impact on health system resources and patient costs. The study is timely given the growing interest in digital healthcare services during the COVID-19 pandemic.

The investigators have considered the potential risks and impacts of COVID-19 on the conduct of this study. We plan to protect the health of participants and study personnel, while also minimising the impact of our study on the provision of health care, by implementing actions that reduce the requirement for face to face visits either temporarily or permanently. These actions will also protect the scientific integrity of the study.

Clinicians will limit patient face-to-face visits by using routinely scheduled visits to identify potential participants, provide an explanation of the research project to allow informed consent, and select a target lesion. These processes may also be achieved in a telehealth consultation where appropriate. We will minimise participant interactions with researchers. Recruitment packages will be emailed, and consent, questionnaires and diaries will be collected online through REDCap. Images will be uploaded into web-based platforms. Researchers will provide information and support by telephone and offer training on the intervention by video web conferencing. We will supply participants with dermatoscopes via couriers. Study staff will work remotely and meet via video web conferencing when public health advice recommend this. An issue related to the scientific integrity of the trial is that there may be more background telehealth use and alternative app use than previously. We plan to collect this information from participants in the baseline and follow-up questionnaires.

In conclusion, this study will contribute novel findings on evidence-based follow-up after treatment of early melanoma, to maximise patient wellbeing and the early detection of new or recurrent melanoma, while minimising costs to the patient and health system.

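### M3 describes the thickness and stage of cancers that were found; its between-arm comparison should be defined over all randomised participants

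*Protocol article*

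**What the plan says.** In the Protocol article, Outcomes {12}, the third secondary outcome reads "M3) Pathological characteristics of new skin cancers: including thickness, stage, and other prognostic factors (melanomas and keratinocyte skin cancers". The unit is the diagnosed cancer. The primary outcome, M1, is worded differently: it is a proportion of participants.

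Trial design {8} states that primary and secondary outcomes in the intervention group, both devices combined, are compared with the control group. Under Statistical methods {20a}, after the time-to-diagnosis model, the text continues: "The appropriate generalised linear model will be used to assess the remaining secondary outcomes". In general this means Poisson models for counts, logistic for proportions and linear for continuous variables. The same section says "All analyses will adhere to the intention-to-treat principle, unless otherwise stated" and refers to a separate SAP for full methods.

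Sample size {14} expects more skin cancers in the patient-led arm, "due to earlier and increased detection in the patient-led group". The figures are "60 events among 300 control participants" and "96 events among 300 intervention participants". On the national rise in melanoma, the Background says "This appears to be largely driven by increased early detection of early-stage melanoma before it has spread from the skin".

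The Discussion says the trial will show "whether patient-led surveillance can safely and effectively enable earlier detection of subsequent new primary or recurrent melanoma and keratinocyte cancers".

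**The concern.** Thickness and stage exist only for people who receive a diagnosis. Diagnosis happens after randomisation, and changing it is the purpose of the intervention. If the arms differ in how many cancers they find, the two groups of cases are no longer comparable by design. A difference in their stage mix can then come from who was added to the cases rather than from any cancer being caught earlier.

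This matters because M1 (diagnosis at an unscheduled visit) and M2 (time to diagnosis) also move in the intervention's favour when more lesions are found, whatever those lesions are. The sample-size text itself combines earlier with increased detection. M3 is the outcome that could show whether less dangerous disease results, and a case-only comparison does not let it do so.

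**Working it through.** **The plan's own figures.** M3 has no stated effect size or sample size. The inputs used here, from Sample size {14}, are consistent with each other: 60/300 = 20%, 96/300 = 32%, 156/600 = 26%. With constant hazards they imply a hazard ratio of ln(0.68)/ln(0.80) = 1.73, close to the stated 1.71. By Schoenfeld's formula, 156 events give 91.8% power for 1.71, so the claim of at least 80% holds. None of these figures is in dispute.

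**Step 1: all skin cancers.** Let *a* be the number of participants with an advanced cancer, the same in both arms. *Advanced* stands for whatever threshold is chosen.

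- Share among cases: *a*/60 in control, *a*/96 in intervention.
- Ratio of shares: (*a*/96)/(*a*/60) = 60/96 = 0.625, a relative fall of 37.5% whatever *a* is.
- Per randomised participant: *a*/300 − *a*/300 = 0.

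The control share is an assumption, shown over a range:

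| Advanced cases per arm | Share of control cases | Share of intervention cases | Per randomised, each arm |
|---|---|---|---|
| 6 | 6/60 = 10% | 6/96 = 6.3% | 2.0% |
| 12 | 12/60 = 20% | 12/96 = 12.5% | 4.0% |
| 18 | 18/60 = 30% | 18/96 = 18.8% | 6.0% |

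**Step 2: the same case-only result under other truths.** Take the middle row.

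- A fall from 20% to 12.5% would also appear with no extra detection and a real reduction: 0.125 × 60 = 7.5 advanced cases, or 2.5% of 300 against 4.0%. The case-only share cannot distinguish this from the zero effect in Step 1; the per-randomised proportion can.
- If the 36 extra cases had the same mix as control, advanced cases would number 12 + 0.20 × 36 = 19.2. The case-only share would be 19.2/96 = 20%, unchanged, while the per-randomised proportion would rise to 19.2/300 = 6.4%.

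So the direction of the distortion depends on the mix of the extra cases.

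**Step 3: melanoma alone.** The protocol assumes 6–8% in control (18–24 of 300) and gives no total melanoma rate for the intervention arm. As an upper case, treat the whole 5-point rise in M1 as new detection, 0.05 × 300 = 15 cases, all in situ. Assume half of control melanomas are in situ.

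- At 6%: 9/18 = 50% against (9 + 15)/33 = 73%; invasive 9/300 = 3.0% in both arms.
- At 8%: 12/24 = 50% against (12 + 15)/39 = 69%; invasive 12/300 = 4.0% in both arms.
- For control in situ shares of 30–70%, the intervention share runs from 57% to 84%.
- As a lower case, if the rise in M1 is only a move from scheduled to unscheduled visits, no cases are added and the mix does not change.

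**The case against.** The strongest reply is that the protocol does not fix a biased analysis. The M3 entry lists characteristics and gives no denominator, effect measure or test. The modelling paragraph's explicit list of continuous outcomes omits thickness, and logistic or Poisson models would suit a per-randomised count equally well. A separate SAP is promised, intention to treat is the general rule, and the numbered secondary objectives do not include pathology. Earlier detection is also addressed by M2, M8 records lesions surgically evaluated, and linked data run to 24 months. A reader given stage counts by arm could divide by the numbers randomised.

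Much of this stands. That M3 would be compared among cases *only* is an inference from its wording, and the SAP could add the missing measure. The 20% and 32% cover keratinocyte cancers as well as melanoma.

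Two stronger readings are tempting and lack support:

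- A reader might infer that M3 will show a false stage benefit. That requires the extra lesions to be mainly early ones. The Background remark on national incidence makes this plausible, but the protocol does not say it of this trial.
- A reader might infer that mean thickness would fall as well. If only in situ lesions are added, it falls only when they are scored as 0 mm, which the protocol does not state. Among invasive melanomas it would not change.

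What does not stand is reliance on the intention-to-treat sentence. It cannot supply a thickness or stage for someone never diagnosed. And what M3 *is* belongs to the outcomes section, which is at hand: it is worded per cancer, it is to be compared between arms, and nothing per randomised participant accompanies it.

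**Conclusion.** The point holds in conditional form. A between-arm comparison of M3 as worded is not a randomised comparison, because the protocol expects the number of diagnosed participants to differ (96 against 60 per 300). If the excess is mainly early lesions and advanced cancers are equally frequent in both arms, the advanced share among cases falls by 37.5% in relative terms with none avoided. If the excess has the same mix as control, the case-only share stays flat while advanced disease per randomised participant rises. The 0.625 factor rests on the protocol's counts for any skin cancer and on the equal-advanced assumption; the melanoma-only shares rest on further assumptions given as ranges.

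The documents do not establish that the analysis will mislead, only that the stated outcome cannot separate earlier detection from additional detection. The primary outcome and the sample size are unaffected. This is a cheap improvement worth making.

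**What to change.** For the between-arm comparison, define M3 over all randomised participants as the proportion in each arm with:

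- (a) any invasive melanoma;
- (b) melanoma at or above a pre-specified thickness or stage, for example the 0.8 mm cut that the Background uses for thin melanoma;
- (c) in situ melanoma only.

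Classify each participant once, by the most serious lesion, and say where recurrences are counted. Report thickness and stage among diagnosed cases as description, without a p value or an effect claim.

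The cost is wording: stage and thickness are already collected and no extra participants are needed. The drawback is low precision. With 9 invasive cases in each arm of 300 (3.0%), the approximate 95% interval for the difference is ±1.96 × √(2 × 0.03 × 0.97/300) = ±2.7 percentage points, and the rarer higher-stage category would be less informative still. If the SAP already contains such measures, it is enough to bring the M3 wording into line with it.
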